### Randomization and blinding

For each participating center a separate randomization list be will prepared by the sponsor to avoid center specific effects and to assure a balanced (1:1) distribution of both treatments within one center (stratification). Randomization lists will be computer-generated using random block lengths.

Randomization is taking place after the patient consented to be part of the clinical investigation (see Fig. 1). Intraoperatively, the sealed opaque envelope containing the information to use either the MXE or the β-PE gliding surface will be opened to randomly allocate the procedure for the specific type of bearing material and to ensure allocation concealment. Whether the study site is using the e.motion PS Pro or the e.motion UC Pro implant is independent from the randomization and according to the standard treatment of each site.

**Fig. 1 Fig1:**
[figure not shown]
Patient inclusion flowchart

While study patients will be blinded, blinding of the surgeon is not possible due to the different color of the implants. Due to the infrastructure and capacity reasons in (some of) the participating study centers, the KSS is recorded by the investigators/surgeons, who typically performed the implantation of the devices. Therefore, blinding of outcome assessors cannot be ensured. The analyzation of radiological results will be performed in a blinded manner.

### Intervention

The implants are CE certified, and the TKA is performed according to the instructions for use. It will be further documented if patella resurfacing is performed, if the image-free navigation system OrthoPilot (Aesculap AG, Tuttlingen) is used, and if implants with or without the advanced surface technology (AS) are used.

In case of an intraoperative finding that the endoprosthesis is not indicated for a specific patient, the patients will be excluded from the study. Surgeries will be performed or, in cases of training procedures, supervised by board certified orthopedic surgeons. All centers meet the certification standards such as the German EndoCert system. Preoperative measures include digital planning of the prosthesis and standardized imaging, antiseptic, and anticoagulation standards. Furthermore, surgical approaches, anesthesia, and tourniquet use are performed according to the standards of each center. Postoperative regimen is not stipulated by the study plan to allow the study centers to follow their standard treatment regimen. It is expected that there are no major differences between the study centers regarding postoperative regimen. There may be minor differences between study centers, but as each study center includes patients in both study groups, the potential for cointervention bias is expected to be small.

Postoperative treatments including standardized weight bearing, physical therapy, anti-thrombotic medication, pain management, and discharge to rehabilitation centers accord to the standard proceeding in each study center. No difference is made between patients of the study groups or other patients not participating in the study.

No restrictions to any concomitant therapy or intervention are defined in this study. No additional surgical or interventional procedure is related to the study.

### Devices

The investigational device is the e.motion UC Pro or PS Pro knee endoprosthesis. The e.motion Pro system is indicated for patients requiring primary surgery. The e.motion UC Pro system is an ultracongruent posterior cruciate ligament retaining design. The e.motion PS Pro is a posterior stabilized posterior cruciate ligament sacrificing design. The size and type of the gliding surface (e.motion UC Pro or e.motion PS Pro meniscus component) depends on the femur component. The tibia has a safety stop which allows ± 30° of rotation. Both variations of the system are used within the study according to the preference and standard of care of the respective investigator and investigational site. Femur and tibia components are made up of a cobalt-chromium-molybdenum alloy. Femur and tibia components are available as AS variants, with a ceramic coating, which reduces wear and release of metal ions into the adjacent tissue and thereby may prevent allergic or hypersensitivity reactions [25–28].

The comparison in this study concerns the material of the gliding surface, either made from UHMWPE blended with 0.1% vitamin E, which is moderately crosslinked with < 50 kGy by γ-irradiation (MXE), or made from ß-sterilized UHMWPE (ß-PE).

### Outcomes

The primary goal of TKA is the restoration of the joint function and the reduction of pain. Measures to analyze these factors are included as outcomes in this study, to be able to compare the investigational device against the comparator.

#### Primary endpoint and measures

The primary endpoint of the study is the functional outcome of the patients 10 years postoperatively. The hypothesis of the study is that the new bearing material MXE is comparable to the established material in terms of performance and safety. Function of the knee after 10 years will be assessed using the KSS. The KSS is an established, examiner-administrated standard clinical evaluation tool reporting results for patients undergoing TKA. It separates findings in the operated knee (kKSS) score from findings related to the patient’s function (fKSS), which might be affected by co-morbidities. The two sub-scores are reported separately ranging from 0 points (worst result) to 100 points (best results), as well as summarized score, total KSS [29]. Final grading of total KSS results scores of 160 to 200 will be rated as excellent, 140 to 159 as good, 120 to 139 as fair, and less than 120 as poor.

#### Secondary endpoints and measures

The following secondary endpoints will be measured to evaluate the safety and performance of the investigational devices.

Preoperatively, data regarding demographics and anamnesis such as age, gender, weight, height, primary diagnosis, concurrent conditions, other joint restrictions, and ASA status will be collected and documented. Intraoperative and surgery-related data (e.g., duration of surgery, anesthesia, blood loss, length of hospital stay, used implant components incl. coating, and intraoperative complications) will also be collected and documented.

Survival of the implant (components) will be analyzed by Kaplan–Meier Analysis [30]. Survival in the sense of this study is defined as removal or exchange of any primary implant component including the removal or exchange of the meniscus component. Secondary interventions at the index knee, e.g., secondary patella replacement, do not count as a revision if no further exchange of the former implant components occur.

Clinical outcome will also be measured with the Oxford Knee Score (OKS), a 12-item, patient-reported questionnaire originally developed and validated specifically to assess function and pain in patients undergoing TKA. It is short, reproducible, valid, and sensitive to clinically important changes over time. OKS ranges from 0 to 48 with 48 being the best outcome [31].

Quality of life of the patients will be analyzed using the 5-dimension 5-level measure of the EuroQol Group (EQ-5D-5L), which is a simple and generic measure for clinical and economic assessment. The questionnaire covers five different dimensions (mobility, self-care, usual activities, pain/discomfort, anxiety/depression) rated in 5 levels (from “the worst health you can imagine” to “the best health you can imagine”) [32]. The questionnaire is filled by the patients themselves.

Radiographic evaluation will be used to evaluate the implant status as well as device condition and potential presence of device-related adverse events including fracture, wear, loosening, or radiolucencies. An external x-ray laboratory will perform the analysis and evaluation of radiographs. In particular, radiolucencies at the interface between the implant and bone, migration of the femur and tibia component in relation to the bone, femoral-tibial angle, mechanical lateral femoral angle, and mechanical medial tibial angle will be analyzed. Furthermore, a new method combining 2-dimensional–3-dimensional registration and artificial intelligence will be applied, which enables accurate determination of changes in the postoperative polyethylene wear in situ. The precision and accuracy of this method is comparable to radiostereometric analysis [33].

Oxidation profile and wear analysis of available retrievals will be analyzed by the biomechanical laboratory of the sponsor. Special focus of these analyses is the oxidation profile, the wear behavior, the mechanics, and the cumulative linear abrasion of these retrievals. These measurements will provide in vivo data regarding the implant material in addition to detailed in vitro data already available [34, 35, 11].

During the course of the study, any upcoming intraoperative or postoperative (serious) adverse device events or effects related or not related to the product under investigation will be documented. The total number of adverse events will be summarized and further evaluated by the sponsor and reported according to local legislation and necessity. Recorded complications will be categorized and analyzed to assess the safety of the investigational product.

In case a patient requires revision of the primary implanted knee endoprosthesis, additional information on the revision surgery will be collected. The reason for revision together with the clinical symptoms shall be documented. Further examinations (e.g., arthroscopy) prior to the revision and the date of revision surgery will be documented. If pre-revision radiographs are taken as part of the clinical routine, the results of the radiographic analysis will be documented.

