**Methods:**

This multicenter, binational randomized controlled trial will enroll patients with knee osteoarthritis eligible for knee arthroplasty with the index device. Patients will be treated with a knee endoprosthesis with either MXE or a standard gliding surface. Patients will be blinded regarding their treatment. After implantation of the devices, patients will be followed up for 10 years. Besides clinical and patient-related outcomes, radiological data will be collected. In case of revision, the gliding surface will be analyzed biomechanically and regarding the oxidative profile.

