### Sample size

The aim of the present study is to show the non-inferiority of the MXE bearing material compared to the β-PE in terms of clinical and functional outcome, which is measured by the KSS. Lizaur-Utrilla et al. showed in their study that the minimally clinically important difference is at least 9 points for the KSS knee (kKSS) and at least 10 points for the KSS function (fKSS) [23]. In order to show non-inferiority of the new material, 10 points were selected as non-inferiority margin for sample size calculation. A recent publication showed that KSS results 5 years after primary TKA vary with a standard deviation of 30 points [24]. Thus, 30 points was used as standard deviation for sample size calculation.

Therefore, a two-sample *t* test with *α* = 0.05 and 80% power and a non-inferiority design (MXE vs. β-PE) with a non-inferiority margin of 10 points requires 224 patients in total (112 patients per group). Assuming a drop-out rate of 20% due to the long-term follow-up, in total 280 patients are necessary to meet the power criteria for the primary endpoint.

As the study includes two variations of the investigational device (e.motion UC Pro and e.motion PS Pro) together with the different bearing materials, in total, 560 patients will be randomized into this study. To avoid center effects, a maximum of 120 patients may be recruited per center. During study preparation, only centers were considered, which are able to recruit a sufficient number of patients according to their throughput of patients.

Patients who withdraw their consent for study participation will not be replaced by new patients. Intraoperative drop-outs due to deviation from the randomization protocol will be replaced by new patients.

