### Data collection, management, statistical analysis and monitoring

The data will be collected by the investigators from routine examinations and documented in an electronic database system. Data entered in the electronic database is pseudonymized using a unique patient identification number to keep the trial patients’ confidentiality. Table 1 shows which data is acquired during the course of the study. In case of death or discontinuation of a patient, it will be inquired whether the knee endoprosthesis was in situ at that time (survival analysis). Trial management, including monitoring of data and data quality, is performed by the sponsor.

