**Table 1 Tab1:**
[figure not shown]
Data acquisition during the course of the study

^*^Required images: knee AP (standing), knee lateral (standing)

^**^Additionally: long leg (standing)

(X): radiographic evaluation may be performed at either visit

There are no specific plans to promote participant retention and complete follow-up. The patients are informed about the follow-up visits before their decision to participate in the study. The visits are kept to a minimum (3 months, 12 months, 5 years, 10 years) and accord to typical follow-up examinations also performed in non-study patients. In addition, patients will receive the OKS self-assessment score at 3 and 7 years postoperatively, to reduce loss-to follow-up rate and allow better monitoring of study patients. Patients will be requested to send the OKS questionnaire back to the study center.

Reasonable effort should be made by the study centers to contact any patient lost to follow-up during the course of the study in order to complete assessments and retrieve any outstanding data and study supplies.

The final programming will be performed after closure of the database by use of an appropriate statistical software package SAS. The sponsor has an overview of results from all participating centers. All data will be analyzed by means of appropriate tables, figures, listings, and statistical tests. Missing data will be analyzed as such and will not be replaced by estimates. The statistical analysis of the primary endpoint has a confirmative character, whereas the secondary endpoints will be analyzed explorative. This must be considered when interpreting the *p*-values and confidence intervals. The description of the patient cohort in means of demographic data and the baseline values of investigated parameters will take place as whole as well as grouped by the therapy group. Analyses will be performed according to the intent-to-treat principle. The consistency of the results will be tested by per-protocol analysis (sensitivity analysis).

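### Kaplan–Meier gives net implant survival; if its complement is read as the patient's 10-year revision risk, that risk is slightly overstated, so report a cumulative incidence beside it

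*Protocol article*

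**What the plan says.** The method is stated in the protocol article under Secondary endpoints and measures: "Survival of the implant (components) will be analyzed by" Kaplan–Meier. The event follows in the next sentence: "Survival in the sense of this study is defined as removal or exchange of any primary implant component". Taken literally, that sentence defines survival as the failure, but the meaning is clear: revision of a component is the event, and death is not part of it.

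The section on data collection, management, statistical analysis and monitoring adds: "In case of death or discontinuation of a patient, it will be inquired whether the knee endoprosthesis was in situ" at that time, and marks this information as meant for the survival analysis.

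Three further facts bear on the point:

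- The Abstract sets the horizon: "After implantation of the devices, patients will be followed up for 10 years".
- The eligibility criteria admit patients from 18 to 80 years and exclude ASA class 3 or higher.
- The statistical text classes the analysis as non-confirmatory: "whereas the secondary endpoints will be analyzed explorative".

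The article does not state a censoring rule for death, and it sets no target, margin or hypothesis for implant survival.

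**The concern.** A patient who dies with the prosthesis in place can no longer be revised. Kaplan–Meier with that patient censored treats the later revision risk as still open and represents it by the patients who remain. With entry up to age 80 and ten years of follow-up, some deaths must be expected, and the gap between the complement of Kaplan–Meier and the proportion revised then has a known direction: upward.

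The article plans to publish results at 1, 5 and 10 years, and readers of a 10-year implant-survival figure commonly turn it into a patient's chance of revision. Kaplan–Meier does not estimate that quantity. What is at stake is how an absolute figure is interpreted, not the test on which the trial's conclusion rests.

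**Working it through.** **The plan's own figures.** None is given for revision or death. The only calculated figure is the sample size for the KSS, based on "0.05 and 80% power and a non-inferiority design". It reproduces with a one-sided 0.05: n per group = 2 × (1.645 + 0.842)² × 30² / 10² ≈ 111.3, rounded up to 112. That gives 224 in total, 224 / 0.8 = 280 with drop-out, and 2 × 280 = 560 for the two implant variants. The present point does not affect it. It supplies one input: 560 / 2 = 280 patients per gliding-surface material.

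**How deaths enter the analysis.** The event is revision only, the estimator is Kaplan–Meier, and implant status is collected at death for that analysis. Under Kaplan–Meier, a death with the implant in situ can then only be a censored observation. This is inferred from the two sections together; it is not stated.

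**The two quantities.** Let H(t) be the cumulative revision hazard and M(t) the cumulative death hazard, with the two independent.

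- The complement of Kaplan–Meier estimates the net risk R = 1 − exp(−H(10)).
- The proportion actually revised is the cumulative incidence, CIF = ∫ exp(−H(t) − M(t)) dH(t) from 0 to 10 years.

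Because exp(−M(t)) is below 1 once deaths occur, CIF is below R.

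**Assumed inputs** (not in the document): R = 5%; 10-year mortality D, absent revision, of 10%, 20% or 30%.

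**Constant hazards.** CIF = H / (H + M) × [1 − (1 − R)(1 − D)], with H = −ln(1 − R) and M = −ln(1 − D). For D = 20%: H = 0.0513 and M = 0.2231, so CIF = 0.0513 / 0.2744 × (1 − 0.95 × 0.80) = 0.1869 × 0.24 = 4.49%.

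**Early revision, late death.** H proportional to (t/10)^0.6 and M proportional to (t/10)^1.5, integrated numerically.

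| D | CIF, constant | Excess of R (points; relative) | CIF, early revision and late death | Excess of R (points; relative) |
|---|---|---|---|---|
| 10% | 4.75% | 0.25; 5.3% | 4.86% | 0.14; 3.0% |
| 20% | 4.49% | 0.51; 11.5% | 4.71% | 0.29; 6.3% |
| 30% | 4.21% | 0.79; 18.7% | 4.55% | 0.45; 10.0% |

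If both hazards rise late with the same shape (1.5), the results equal the constant-hazard column. Over a wider grid (R from 2% to 10%, D from 5% to 40%) the excess runs from 0.03 to 2.13 points.

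**Against sampling error.** The approximate 95% half-width for a 5% risk in 280 patients is 1.96 × √(0.05 × 0.95 / 280) = 2.6 points. This ignores censoring, so the real interval would be wider.

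**Between arms.** For net risks of 5% and 8% with the same mortality in both arms, the risk ratio is 0.05 / 0.08 = 0.625 by Kaplan–Meier. From the cumulative incidences under constant hazards it is 0.6248, 0.6246 and 0.6244 at 10%, 20% and 30% mortality.

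**The case against.** The strongest reply is that Kaplan–Meier is not wrong here. The trial compares two materials, and net implant survival is a legitimate measure of a material's durability when death is independent of revision. The cumulative incidence answers a different question. This stands, and it rules out the stronger reading that the published 10-year revision risk will be overstated. Nothing in the article says that the complement of Kaplan–Meier will be presented as the share of patients revised.

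A reader might also infer that implant survival is the trial's main safety figure. The article does not say so: it is one secondary endpoint among several, beside adverse events, complications and radiographic findings.

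A third inference would be that the comparison of materials is biased. It hardly moves with equal mortality, and nothing in the article suggests that mortality would differ by gliding surface.

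The size is also modest. The article plans for 20% drop-out from all causes and excludes ASA class 3 or higher. The drop-out figure is a planning assumption and not a bound on mortality, but it is the only anchor available. At 20% mortality and a 5% net risk the excess is 0.29 to 0.51 points, well inside sampling error.

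Finally, an analysis plan that is not shown may already include a competing-risk analysis, and the article does not say that Kaplan–Meier will stand alone. The point is therefore not that something is missing. The article does fix the estimator and the event, and for the absolute revision risk a better-suited estimator can be added from data already to be collected.

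**Conclusion.** The point holds as a minor one. As the article reads, deaths with the implant in situ are in effect censored. The Kaplan–Meier curve is then valid for net implant survival, and its complement exceeds the actual 10-year probability of revision.

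With an assumed net risk of 5% and assumed mortality of 10% to 30%, the excess is about 0.1 to 0.8 percentage points, or 3% to 19% relative. It is smaller than the sampling error of a single arm, but it is systematic and always in the same direction. These figures rest on assumed rates, independence of death and revision, and the hazard shapes shown. The inference that deaths are censored also comes from reading two sections together.

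The between-arm comparison is practically unchanged. The confirmatory KSS test and the sample size are not affected.

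**What to change.** In the analysis plan, before the 10-year data exist:

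- State that death is a competing event when the absolute revision risk is estimated.
- Report the Aalen–Johansen cumulative incidence of revision per arm, with its confidence interval, beside the Kaplan–Meier curve.
- Label the Kaplan–Meier curve as net implant survival and keep it for comparison with the literature.
- Keep the between-arm comparison on the cause-specific hazard. It also censors deaths, which is appropriate for comparing the revision rates of two materials.

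The cost is a few lines of SAS code and a sentence or two of wording. No new data are needed, because implant status at death is already to be asked for. The downside is one extra curve to explain.

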### Data collection, management, statistical analysis and monitoring

The data will be collected by the investigators from routine examinations and documented in an electronic database system. Data entered in the electronic database is pseudonymized using a unique patient identification number to keep the trial patients’ confidentiality. Table 1 shows which data is acquired during the course of the study. In case of death or discontinuation of a patient, it will be inquired whether the knee endoprosthesis was in situ at that time (survival analysis). Trial management, including monitoring of data and data quality, is performed by the sponsor.

**Table 1 Tab1:**
[figure not shown]
Data acquisition during the course of the study

^*^Required images: knee AP (standing), knee lateral (standing)

^**^Additionally: long leg (standing)

(X): radiographic evaluation may be performed at either visit

There are no specific plans to promote participant retention and complete follow-up. The patients are informed about the follow-up visits before their decision to participate in the study. The visits are kept to a minimum (3 months, 12 months, 5 years, 10 years) and accord to typical follow-up examinations also performed in non-study patients. In addition, patients will receive the OKS self-assessment score at 3 and 7 years postoperatively, to reduce loss-to follow-up rate and allow better monitoring of study patients. Patients will be requested to send the OKS questionnaire back to the study center.

Reasonable effort should be made by the study centers to contact any patient lost to follow-up during the course of the study in order to complete assessments and retrieve any outstanding data and study supplies.

The final programming will be performed after closure of the database by use of an appropriate statistical software package SAS. The sponsor has an overview of results from all participating centers. All data will be analyzed by means of appropriate tables, figures, listings, and statistical tests. Missing data will be analyzed as such and will not be replaced by estimates. The statistical analysis of the primary endpoint has a confirmative character, whereas the secondary endpoints will be analyzed explorative. This must be considered when interpreting the *p*-values and confidence intervals. The description of the patient cohort in means of demographic data and the baseline values of investigated parameters will take place as whole as well as grouped by the therapy group. Analyses will be performed according to the intent-to-treat principle. The consistency of the results will be tested by per-protocol analysis (sensitivity analysis).

The study hypothesis will be tested using a two-sample *t* test. The results of the KSS Score will be analyzed as sum of the sub scores fKSS and kKSS. Primary testing will be done comparing the MXE with the β-PE group. Comparison between the different implant types might be done exploratively. Each implant variation (UC Pro vs. PS Pro) will be tested individually for primary endpoint analysis. Secondary endpoints will be tabulated as frequencies and rates/results respectively as means and standard deviations. Confidence intervals will be used when appropriate.

An explorative interim analysis of secondary objectives will be done 1 and 5 years postoperatively. It is intended to publish the 1-year as well as the 5- and 10-year results in a peer-reviewed journal in order to contribute to publicly available knowledge. Furthermore, the study and (intermediate) results may be presented on scientific conferences. Therefore, data of all available patients and centers shall be included. Manuscripts shall be reviewed and approved by all participating study centers. In case that the study results cannot be published in a peer-reviewed journal (e.g., due to non-significant results), a manuscript shall be deposited in a preprint archive. Furthermore, a study report will be attached to the ClinicalTrials.gov entry of this study.

Authorized, qualified representatives of the sponsor or designated personnel of a contract research organization will perform monitoring visits at investigational sites in regular intervals to verify adherence to protocol and local legal requirements, to perform source data verification and to assist the investigator in study related activities. Approximately one visit per site and year is planned, with more visits in the beginning of the study. As a risk-based approach, discovered deviations from the study protocol may increase the number or intensity of monitoring visits. Site audits are not generally planned. If monitoring activities reveal the necessity, e.g., due to severe deviations from GCP principles, site audits may be performed.

Vendors employed for the study were audited and approved by the processes of the sponsor supplier quality management.

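### The no-replacement rule makes the 10-year primary test an available-case analysis, which does not match the declared intent-to-treat principle, and the one sensitivity analysis named does not address missing outcomes

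*Protocol article*

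**What the plan says.** Three statements in the protocol article together fix the primary analysis. Primary endpoint and measures sets the endpoint as function at 10 years, measured by the KSS. Data collection, management, statistical analysis and monitoring names a two-sample t test on the sum of the two KSS sub-scores. The same section adds: "Missing data will be analyzed as such and will not be replaced by estimates".

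That section also declares: "Analyses will be performed according to the intent-to-treat principle". The only sensitivity analysis it names is per-protocol.

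The Sample size section builds in the expected loss: "Assuming a drop-out rate of 20% due to the long-term follow-up". It inflates 224 evaluable patients to 280 for one comparison and doubles this to 560 for the two implant variants.

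On follow-up the article says: "The visits are kept to a minimum (3 months, 12 months, 5 years, 10 years"). It describes no dedicated retention programme beyond mailed Oxford Knee Score questionnaires at 3 and 7 years and a request that centres try to reach lost patients. Revisions are documented, and implant survival is a secondary endpoint analysed by Kaplan–Meier. No rule is given for the 10-year KSS of a patient who has been revised or has died.

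**The concern.** A t test on 10-year KSS has no place for a patient without a 10-year KSS. With replacement ruled out, that patient leaves the confirmatory comparison, whatever was recorded at earlier visits. The analysis called intent-to-treat is therefore expected to omit one randomised patient in five. Inflating the sample size restores power but does not protect against bias.

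The per-protocol analysis does not help. It can only remove further patients and says nothing about those without an outcome.

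In a non-inferiority trial what matters is whether loss is related to outcome differently in the two arms. If more MXE knees fail, or fail worse, and those patients are not scored at 10 years, the remaining MXE patients look closer to control than the randomised group really is. Survival analysis might show an imbalance in revisions, but secondary endpoints are declared exploratory and would not change the primary conclusion.

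**Working it through.** **Inputs from the Sample size section.** Error rate and power: "0.05 and 80% power and a non-inferiority design (MXE vs. β-PE"). Margin: "10 points were selected as non-inferiority margin for sample size calculation". Standard deviation: "30 points was used as standard deviation for sample size calculation". Result: "with a non-inferiority margin of 10 points requires 224 patients in total (112 patients per group").

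**Reproducing the plan's figure.** n per group = 2 × (1.645 + 0.842)² × 30² / 10² = 111.3, rounded up to 112, so 224 in total. The exact t-test power at 112 per group is 80.0%. A one-sided 2.5% level would need 142 per group, so the stated 5% is one-sided. Then 224 / 0.8 = 280, and 2 × 280 = 560. The planned figures are correct.

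**Planned loss.** Per variant, 280 / 2 = 140 are randomised per arm and 112 analysed, so 28 per arm are absent. Over both variants this is 112 of 560. This assumes that each variant recruits 280 and that loss is equal between arms.

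**Decision threshold.** SE = 30 × √(2/112) = 4.01. Non-inferiority is declared when the observed difference (MXE minus β-PE) exceeds -10 + 1.645 × 4.01 = -3.41.

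**Completers against all randomised.** With 20% missing in each arm,

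D(all) = 0.8 × D(completers) + 0.2 × D(missing).

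Set D(all) = -10, the margin, where the test should declare non-inferiority 5% of the time. Then D(completers) = (-10 - 0.2 × D(missing)) / 0.8, and the false non-inferiority rate is P(Z > 1.645 - (D(completers) + 10) / 4.01).

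| D(missing), assumed | D(completers) | Shift | False non-inferiority rate |
|---|---|---|---|
| 0 | -12.5 | -2.5 | P(Z > 2.27) = about 1% |
| -10 | -10.0 | 0 | 5% |
| -20 | -7.5 | 2.5 | P(Z > 1.02) = about 15% |
| -26 | -6.0 | 4.0 | P(Z > 0.65) = about 26% |

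The bias depends on how the gap among the missing compares with the gap among completers. When the two are equal there is none.

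**Same question in terms of failures.** Suppose failed knees are the unmeasured ones and would score G points below the completers of their arm. The hidden shift is then (failure share in MXE - failure share in β-PE) × G. With 10% against 5% failing and G = 40, 60 or 80, the shift is 2, 3 or 4 points and the error rate 12.6%, 18.5% or 25.9%. With 5% in each arm it stays at 5.0%. With 5% in MXE against 10% in β-PE it falls to 1.6%, 0.8% or 0.4%.

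**How far a result could be tipped.** If the observed completer difference is 0 and missing MXE patients are worsened by an amount δ, the estimate moves by 0.2 × δ. It reaches the threshold of -3.41 at δ = 3.41 / 0.2 = 17 points, with the SE held at 4.01.

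The documents give no failure rates and no score gaps. All values of D(missing), failure share and G are assumptions.

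**The case against.** The strongest defence has four parts.

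First, a reader might infer that the plan drops failed or revised knees. No section says so. Revision is not listed as a reason for discontinuation, extra data are collected after it, and a revised patient who attends at 10 years can have a KSS. Under intent-to-treat that score counts. This stands: the gap is an absent rule, not a stated exclusion.

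Second, a reader might infer that the bias necessarily favours non-inferiority. It does not. The direction depends on which arm loses more or worse failures, and the Discussion expects MXE to be less sensitive to wear and creep. This also stands. However, the Discussion itself leaves open whether less wear improves outcome or survival, and a non-inferiority test has to hold its error rate when the new material is worse.

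Third, the 20% is a general drop-out assumption, not a revision rate or a minimum loss, and the sample size allows for it correctly. The mailed questionnaires and contact attempts may reduce it, and implant status is sought at death or discontinuation. All true, but none of this changes who enters the primary test.

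Fourth, missing-data detail usually belongs in the analysis plan, which is not shown. That would answer silence, but here the protocol states a rule. An analysis plan that imputed would contradict the rule, and one that used a repeated-measures model would contradict the named t test. It could add sensitivity analyses without conflict.

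**Conclusion.** The concern holds in this form. The no-replacement rule and the t test on 10-year KSS make the confirmatory test an available-case analysis, with 28 of 140 patients per arm per variant assumed lost. This does not match the declared intent-to-treat principle, and the named sensitivity analysis does not address missing outcomes.

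The consequence is conditional. At a true all-randomised difference of -10, one-sided 5% and 20% missing per arm, a 20-point deficit of missing MXE patients against missing controls raises the false non-inferiority rate to about 15%, and a 26-point deficit to about 26%. A 10-point deficit leaves it at 5%, and a smaller one lowers it. These figures show how sensitive the test is; they do not predict this trial's error rate.

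**What to change.** - **Primary analysis.** Replace the t test by the 10-year MXE minus β-PE contrast from a mixed model for repeated measures (or a constrained longitudinal model) on all scheduled KSS values. No value is imputed, and patients with earlier scores but no 10-year score contribute. This assumes that KSS is recorded at the interim visits (Table 1 is not shown) and that data are missing at random. The model does not by itself remove loss that depends on unobserved outcomes.
- **Revision and death.** State that an observed 10-year KSS after revision stays in the intent-to-treat analysis, and state how deaths are treated. Do not carry forward the last pre-revision KSS: with visits at 12 months and 5 years, a knee revised in year 4 could enter with a good 12-month score, and an observed later score would be overridden.
- **Sensitivity analyses.** Add a tipping-point analysis that worsens missing MXE values until -10 is no longer excluded, and an analysis that assigns a pre-stated unfavourable score to revised knees. Keep the per-protocol analysis for its own purpose.

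The cost is an amendment to the protocol and analysis plan, and a slightly more complex model. No new visits are needed if KSS is already taken at the interim visits. Trial status gives first inclusion in March 2021 and last patient out in Q4 2033, so the change can be made before 10-year data exist.
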